### Conversion to Manual Procedure Data Collection

The Investigator shall determine if it is necessary to convert to standard manual percutaneous techniques to complete the PCI. The Investigator should make this decision based on his/her medical assessment of the situation in accordance with the best interest of the participant. It is recommended that conversion to manual operation be performed at the discretion of the Investigator or if any of the following occur:

- The inability to navigate the guidewire or balloon/stent catheters using the CorPath GRX System as intended.
- Any clinical condition that requires rapid medical intervention.

The reason for conversion to manual should be reported by the operator and documented.

### Partial Robotic Assistance Data Collection

All planned and unplanned partial robotic assistance, e.g. rotational atherectomy, IVUS, etc., will be documented. The investigator will indicate whether the manual part of the procedure was planned, e.g. lesion prep done with OTW system or unplanned, e.g. stent was undeliverable due to severe calcification requiring rotational atherectomy.

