## **Technical Success**

Defined as successful completion of the PCI absent *unplanned* conversion to manual operation of guidewire or balloon/stent catheter or inability to navigate vessel anatomy or poor guide catheter support.

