### Data to be collected prior to initiating PCI

- Operator and assistant details
- Arterial access site and side
- Procedure start time (Sheath insertion)
- PCI Start Time (Guide Catheter Insertion)
- American Heart Association/American College of Cardiology lesion classification

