### Data to be collected during the procedure

- Guidewire activation to guidewire retraction
- Fluoroscopy time
- Participant and staff radiation exposure (dose area product (DAP) and air kerma (AK))
- Lesion characteristics (eg tortuosity, calcification and bifurcation)
- Operator assessment of stent length
- Robotic assessment of stent length
- Contrast volume
- Procedure end time (Guide Catheter out)
- Equipment utilisation
- Pre and post PCI stenosis percentage
- Need for manual input (if required) and reason for this
- Number of times stent visualisation technique (eg stent boost or clearstent) used
- Use of robotic algorithms (techIQ) to assist lesion navigation
- Any adverse events
- Use of intracoronary physiology and/or intracoronary imaging
- Operator survey of task load

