# Data Management, Statistical Analysis and Record Keeping

## **Statistical Methods**

This is a double-arm, open-label, randomized controlled trial of the CorPath GRX System designed to evaluate the safety and effectiveness of the clinical and technical performance of the CorPath GRX System in the delivery and manipulation of coronary guidewires and stent/balloon catheters, and remote manipulation of guide catheters for use in PCI in comparison to standard of care. The analysis of data collected as part of the RCT will include, but may not be limited to, the Objectives and Measures outlined in Section 3.0 of this protocol. Continuous variables will be summarized using the number of observations, mean, standard deviation, median, min and max values. Categorical variables will be summarized with the number and percent in each category out of the number observed. Two-sided 95% confidence intervals may be calculated and two-sided p-values < 0.05 will be considered statistically significant.

The outcome of patient radiation exposure will be analysed using variance (ANOVA). As each participant may have multiple lesions, the outcome of clinical success at day 3 will be analysed using a two level multilevel models. Logit link will be used with a binomial distribution and restricted maximum likelihood (REML) will be used for estimation. Predictor variables in the models will include treatment group.

Technical success will analysed with Fisher’s exact test, comparing the proportion of participants with technical success between the two groups. Logistic regression will be used to compare technical success accounting for lesion complexity. For all other secondary outcomes, continuous outcomes will be measured using independent t-test (or non-parametric alternative depending on distributional assumptions), and categorical outcomes analysed by Fisher’s exact test. For outcomes measured repeatedly over time, multilevel models with an appropriate link functions will be used for analysis.

All statistical analyses will be performed using SAS software (version 9.4) or other widely accepted statistical or graphical software.

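### Technical success turns on whether a manual step was planned, but the unblinded investigator may set that label at any time, with no pre-procedure record and no stated independent review

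*Protocol*

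**What the plan says.** Section 2.3 (Technical Success) requires "successful completion of the PCI absent *unplanned* conversion to manual operation of guidewire" or balloon/stent catheter, and then continues "or inability to navigate vessel anatomy or poor guide catheter support". The trial summary repeats the definition and emphasises the same adjective. Technical performance is named in the primary objective (Section 2.1).

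Section 7.2.7 (Partial Robotic Assistance Data Collection) asks for all planned and unplanned partial robotic assistance to be documented and says "The investigator will indicate whether the manual part of the procedure was planned". It gives one example of each label. The planned example is lesion preparation with an over-the-wire system; the other reads "unplanned, e.g. stent was undeliverable due to severe calcification requiring rotational atherectomy". There is no rule and no time by which the plan must be fixed.

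Section 7.2.2 lists five items to collect before PCI: operator and assistant, access site, two start times, and "American Heart Association/American College of Cardiology lesion classification". Section 7.2.3 lists, among data collected during the procedure, "Need for manual input (if required) and reason for this". Section 7.2.6 has the operator report why a case was converted.

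Section 8.1 states: "This is a double-arm, open-label, randomized controlled trial of the CorPath GRX System". It compares technical success between arms by Fisher's exact test, with a logistic regression for lesion complexity. Section 5.3 has the investigator told the allocation. The independent committee in Section 10.2 reviews clinical events, and the event assessments sent to adjudication under Section 7.7.2 are those meeting the MACE definition.

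**The concern.** An endpoint component should be classified by a rule, or from information fixed before the outcome is known. Here the classification rests on the operator's intention, and the protocol does not require that intention to be written down beforehand. Section 9.2 restricts robotic PCI to trained investigators, so the person who gives the label may be the person who ran the case. Nothing requires it to be anyone else.

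The exposed cases are those in which the same manual work could fit either label. In a calcified lesion, manual preparation may have been intended from the angiogram, or adopted after a robotic attempt failed. The first is compatible with technical success and the second is not. What separates them is when the decision was made, and that time is not a required data item.

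The direction of any error is fixed. A standard PCI cannot convert to manual operation, so this component can produce failures in the robotic arm only. Labelling an unplanned step as planned can only raise the robotic-arm rate. If the intention is not recorded at the time, no later analysis can recover it.

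**Working it through.** **1. The plan's own figure.** The protocol gives no technical success rate and no power for this endpoint. Its only sample-size statement (Section 8.1) concerns patient radiation: control mean 1284 mGy, SDs 180 and 142.83, a 20% reduction, 150 per arm, two-sided 5%.
- Difference = 0.20 × 1284 = 256.8 mGy.
- Common SD = √[(180² + 142.83²)/2] = 162.48.
- Noncentrality = 256.8 / (162.48 × √(2/150)) = 13.69, giving power above 99.9%.

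The stated power of more than 99% is reproduced. It says nothing about technical success and is unaffected by this point.

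**2. Does the label have a safeguard?**

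| Possible safeguard | Where it would be | What is there |
|---|---|---|
| Intended manual steps recorded beforehand | 7.2.2 | Five items, none on manual steps |
| Time limit for the label | 7.2.7 | None |
| Decision rule | 7.2.7 | One example of each label, no rule |
| Blinded or separate assessor | 5.3, 8.1 | Open-label; investigator knows the arm |
| Independent review | 7.7.2, 10.2 | Clinical events and MACE; conversion not named |
| Record of the manual step and its reason | 7.2.3, 7.2.6, 7.2.7 | Present, reported from the operator's side |

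Only the last exists. It supports a partial audit but does not fix the label.

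**3. Effect per case.** One relabelled case is 1/150 = 0.67 percentage points of the robotic-arm rate. As an illustration, assume 15 of 150 robotic cases need a manual step because of difficulty. True success is 135/150 = 90.0%. Relabelling 5 gives 140/150 = 93.3%, and relabelling 10 gives 145/150 = 96.7%. Both the 15 and the fractions relabelled are assumptions.

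**4. Effect on the Fisher comparison.** With 0 control failures and k robotic failures at 150 per arm, the two-sided p-value is 2 × C(150,k)/C(300,k).
- k = 6: p = 0.030; k = 5: p = 0.060.
- With 1 control failure: 8 robotic failures give p = 0.036, and 7 give p = 0.067.

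At these thresholds, one relabelled case changes the significance of the result.

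**5. Range under assumed rates.** Power is the sum, over all pairs of binomial failure counts, of their joint probability where Fisher's p < 0.05. The table assumes that half of the true robotic failures are relabelled as planned. Arrows run from no relabelling to half relabelled.

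| Assumed robotic failure | Observed success | Power, control failure 0% | Power, control failure 1% |
|---|---|---|---|
| 5% | 95.0 → 97.5% | 77 → 18% | 40 → 5% |
| 8% | 92.0 → 96.0% | 98 → 56% | 81 → 23% |
| 10% | 90.0 → 95.0% | 99.8 → 77% | 94 → 40% |
| 15% | 85.0 → 92.5% | >99.9 → 97% | 99.8 → 76% |

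The table shows how sensitive the comparison would be. It does not predict how often relabelling would happen. It also treats every robotic failure as one that rests on the label alone, which Section 2.3 may not allow (see the objection).

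**The case against.** Four points can be made for the plan.

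First, the label may not decide the endpoint alone. Section 2.3 also names navigation failure and poor guide catheter support. On a natural reading these defeat technical success whatever the manual step is called. A reader might infer that a wire that would not cross robotically could be hidden by calling the manual step planned. The documents do not support that: such a case looks like a navigation failure, and Section 7.2.6 names this difficulty as a reason to convert. This stands in part. The sentence does not settle whether the two grounds are independent or are qualified by the conversion clause.

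Second, a reader might infer that relabelling could never be detected. That is too strong. Manual input and its reason are recorded (7.2.3, 7.2.6), partial assistance is documented under either label (7.2.7), and moves from robotic to standard technique are captured (2.6). An analysis counting every manual conversion as a failure could be run on these data and would bound the effect. This stands. But the bound would also fail steps that really were planned, and the recorded reason comes from the same operator.

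Third, the examples in Section 7.2.7 give some guidance, and lesion preparation chosen after difficulty resembles the unplanned one. True, but two examples are not a rule, and the timing that separates them is not captured. The past tense in that section proves little either way: no entry time is set, and the eCRF, which is not shown, might contain a prospective field. The protocol does not require one.

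Fourth, the sensitivity analysis may belong in an SAP that is not shown. That is fair for the analysis. It does not cover the data collection, which the protocol itself must fix.

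**Conclusion.** The point holds as a weakness in how the endpoint is classified. A label that can decide technical success is given by an unblinded investigator, with no time limit, no prior record and no stated independent review. Any misuse could only favour the robotic arm.

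It does not follow that technical success will be biased upward. The documents show that relabelling is possible, not that it happens. The exposure is limited to failures that rest on the conversion clause alone, and how many those are depends on how the ambiguous wording of Section 2.3 is read.

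The size cannot be estimated from the protocol. The firm figure is 0.67 percentage points per relabelled case, given 150 in the robotic arm; all failure rates and relabelled fractions above are assumptions. The change should be made: it is cheap before the cases are done, and the missing information cannot be recovered afterwards.

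**What to change.** - **Section 7.2.2:** for robotic-arm cases, add a time-stamped EDC field listing the steps intended to be manual, or none. Lock it after target-lesion angiography and before the coronary guidewire is introduced, that is, between steps 3 and 4 of Section 7.2.5. Locking it before guide catheter insertion would be too early, since steps properly planned from that angiogram would then count as failures.
- **Sections 2.3 and 7.2.7:** state that, for endpoint classification only, manual operation of the guidewire or balloon/stent catheter that is not on the locked list is unplanned and counts as technical failure. The operator still gives the reason but does not choose the label.
- **Section 2.3:** state that navigation failure and poor guide catheter support are failures in their own right, whatever the label.
- **Analysis:** add a sensitivity analysis counting every manual conversion as a failure, reported beside the main result as a bound.

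The operator's freedom to convert under Section 7.2.6 is unchanged. The cost is one extra field and a few sentences of protocol text. Reported technical success may be slightly lower, because a step that becomes sensible mid-case would count as unplanned.

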### Post-Procedure Data Collection

**Acute Post Procedure Medication Regimen**

- Follow standard operator and institutional routines for recommended anticoagulation and anti-platelet regimens.

**Post Procedure Participant Evaluations**

- Clinical assessment and physical examination
- Record of all adverse events as described in Section 7.7
- If clinically indicated as determined by the investigator
  - 12-lead ECG
  - CK, CK-MB and/or Troponin

## **Day 3 or Discharge**

The following evaluations are to be performed post the Index procedure on Day 3 or discharge (whichever is sooner):

- Complete physical exam
- Complete vital signs (heart rate, blood pressure)
- Medication assessment
- 12 lead electrocardiogram
  - Blood assays for full blood count, renal function, cardiac enzymes, creatine kinease (CK) & creatine kinease myocardial band (CK-MB) and/or Troponin
- Adverse event assessment as described in Section 7.6
- Event assessment

## **Day only PCI patients**

Some patients will be suitable for same day discharge as their PCI procedure. In this instance, they will be asked to return the next day to the cathether laboratory clinic for a medical review as detailed in Section 7.3.

## **Day 30**

The following evaluations are to be performed post the Index procedure on Day 30 ± 5 days:

- Medication assessment
- Adverse event assessment as described in Section 7.6
- Event assessment

## **Day 365 or End of Study (EOS)**

The following evaluations are to be performed post the Index procedure on Day 365 ± 14 days or EOS:

- Medication assessment
- Adverse event assessment
- Event assessment

## **Adverse Events, Event Assessment and Serious Adverse Device Events**

### Adverse Events (AEs)

Study staff will closely monitor each participant for the development of device and/or procedure related adverse events. Adverse events that meet this criteria will continue to be monitored until day 30 or until resolution or the investigator deems them stable and unresolved.

Adverse Events of Special Interest (AESI) are those defined as MACE including cardiac death, clinically relevant MI after coronary revascularization (Q-wave or non-Q-wave myocardial infarction), or clinically driven target vessel revascularization (TVR).

### Event Assessments

This study is not using any unregistered products therefore only serious adverse events that meet the MACE definition will be reported from visit 2 until the end of study visit (visit 5). Event Assessments will be reviewed by the End-Point Adjudication Committee.

**Major Adverse Cardiac Event (MACE):** MACE is defined as cardiac death, Q-wave or non Q-wave myocardial infarction (MI), or clinically driven target vessel revascularization (TVR) by percutaneous or surgical methods.

**Cardiac Death:** Death due to cardiac causes. If the cause of death cannot be determined, it will be categorized as cardiac.

Myocardial Infarction (Protocol Definition):

Clinically relevant MI after coronary revascularization will be defined by the 4^th^ Universal Definition of PCI related MI. Events as defined by the Society for Cardiovascular Angiography and Interventions definition for periprocedural MI will also be recorded.

The 4th Universal Definition of PCI related MI defines:

- Participants with normal baseline cardiac biomarkers
  - Cardiac troponin (cTN) >5x the 99^th^ percentile of upper reference limit (URL)
- Participants with elevated baseline cardiac biomarkers
  - Rise in post procedure cTN by >20% and be at least >5x 99^th^ percentile of URL AND
  - At least one of the following
    - New ischaemic ECG changes
    - Development of new pathological Q waves
    - Imaging evidence of new loss of viable myocardium or new regional wall motion abnormality in a pattern consistent with an ischaemic aetiology
    - Angiographic findings consistent with a procedural flow limiting complication such as coronary dissection, occlusion of a major epicardial artery or a side branch occlusion/thrombus, disruption or collateral flow or distal embolisation

The Society for Cardiovascular Angiography and Interventions definition for periprocedural MI defines:

- Participants with normal baseline cardiac biomarkers
  - CK-MB >10x upper limit normal (ULN) or cTn (I or T) >70x ULN, or
  - CK-MB >5x ULN or cTn >35x ULN plus new Q-waves in >2 contiguous leads or LBBB
- Participants with elevated baseline cardiac biomarkers
  - Baseline biomarkers are stable or falling:
    - CK-MB >10x ULN or cTn (I or T) >70x ULN of **most recent pre-procedure level**, or
    - CK-MB >5x ULN or cTn >35x ULN of **most recent pre-procedure level** plus new Q-waves in >2 contiguous leads or LBBB
  - Baseline biomarkers have not been shown to be stable or falling: CK-MB (or cTn) rises by an absolute increment equal to those recommended above plus new ST-segment elevation or depression plus signs consistent with a clinically relevant MI, such as new onset or worsening heart failure or sustained hypotension.

**Target Vessel Revascularization (TVR):** Ischemia-driven repeat percutaneous intervention of the target vessel or bypass surgery of the target vessel. A TVR will be considered as ischemia-driven if the target vessel diameter stenosis is
[figure not shown]
≥50% and any of the following are present:

- A positive functional study corresponding to the area served by the target vessel.
- Ischemic ECG changes at rest in a distribution consistent with the target vessel.
- Ischemic symptoms referable to the target lesion.

**In-Hospital MACE:** MACE that occurs within 72 hours of the procedure or prior to hospital discharge, whichever occurs first, in a participant treated with the CorPath GRX System.

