## **Randomisation**

Participants will be randomized 1:1 to the PCI performed using standard care or technology-assisted PCI in blocks to ensure balanced distribution of the treatment groups at all times. The study team will enter the participant screening information into the electronic data capture (EDC) system after informed consent has been obtained. Once the participant is determined to be eligible prior to the Index Procedure the study team will randomise the participant using the EDC. The Investigator will be advised of this and the allocated method of PCI will be performed. The participant will ideally remain blinded to the method of PCI performed.

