## **Study Endpoint Event Adjudication**

An independent events committee will review all clinical events associated with the study endpoints. Adjudication will be based on narratives and source data supplied by the sites. Source data that may be collected for review include, but are not limited to, de-identified angiograms (diagnostic and procedural), catheterization lab report, procedure report, discharge summary, lab reports, and pre- and post-procedure ECGs. The site may be contacted for queries and additional support documentation.

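### Serious-event reporting is limited to events already judged to be MACE by a site that knows the arm, so adjudication has no assured route to events the site rejects

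*Protocol*

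**What the plan says.** Protocol Section 7.7.2 (Event Assessments) sets the reporting rule: "therefore only serious adverse events that meet the MACE definition will be reported from visit 2 until the end of study visit (visit 5". The next sentence says what the committee gets: "Event Assessments will be reviewed by the End-Point Adjudication Committee".

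Section 10.2 (Study Endpoint Event Adjudication) describes a wider remit: "An independent events committee will review all clinical events associated with the study endpoints". It also says where the material comes from: "Adjudication will be based on narratives and source data supplied by the sites". Section 2.4.2 promises a summary of every SAE from the procedure to study end, and Section 7.8.2 says that the study needs no SAE reporting.

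On blinding, Section 8.1 states: "This is a double-arm, open-label, randomized controlled trial of the CorPath GRX System". Section 5.3 says of the allocation: "The Investigator will be advised of this and the allocated method of PCI will be performed".

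There is a second stream of events. Section 7.7.1 says: "Study staff will closely monitor each participant for the development of device and/or procedure related adverse events". Footnote 5 to the Schedule of Events (Section 3.3) scopes the post-index event assessments as procedure-related, intervention-related or MACE. Sections 7.2.3 and 7.2.8 collect adverse events during and after the procedure, and Section 7.8.1 asks for a separate form for each event.

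**The concern.** Whether an event is MACE is often a judgement: whether a death is cardiac, whether a biomarker rise is a new infarction, whether a repeat revascularisation is ischaemia-driven. An independent committee exists to make those calls. If an event must already meet the definition before it is reported, the call is made first by people who know which arm the participant was in, and the committee reviews what remains.

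MACE at 30 days and 1 year is a stated safety measure. Any difference between arms in how readily the site labels events would enter that comparison, and a committee that sees only forwarded events could not correct it. A later SAP or committee charter could not recover events that the protocol tells the site not to report.

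**Working it through.** **Step 1: who applies the definition.** Section 7.7.2 makes meeting the MACE definition a condition of reporting. The protocol does not name who decides, but only the site sees the event at that stage. By Sections 5.3 and 8.1 the site knows the arm. By Section 10.2 the committee works from what the site sends. The protocol describes no list of suspected events, no central screening of laboratory or readmission data, and no review of unreported events. The record check in Section 6.2 applies only after a missed visit and asks whether the participant is alive.

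**Step 2: follow three kinds of event through the rules.**

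- *Death at month 8, called non-cardiac by the site.* It is not site-judged MACE, so Section 7.7.2 does not report it. It is unlikely to be called device- or procedure-related, so Section 7.7.1 and footnote 5 do not capture it either. The rule that a death of undetermined cause counts as cardiac cannot be applied by a committee that does not see the case.
- *Repeat PCI at month 6, called not ischaemia-driven.* The outcome is the same.
- *Biomarker rise during the index admission, not called MI.* Sections 7.2.3, 7.2.8, 7.7.1 and 7.8.1 give a route to a form. The protocol does not say whether such forms go to the committee. Relatedness is itself the investigator's judgement (Section 7.7.4).

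Section 7.6 also lists an adverse event assessment at Day 365, without stating its scope. The schedule, however, marks the adverse event row only at the index procedure. That is not an assured route for late unrelated events.

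**Step 3: which endpoint is exposed.** Clinical success (Section 2.2.1) uses in-hospital MACE only, which falls in the window with the partial separate route. The unprotected period is after discharge, so the exposure is mainly 30-day and 1-year MACE.

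**Step 4: illustration of size.** There is no MACE figure in the protocol to reproduce; its sample size rests on radiation exposure. The only input from the document is 150 participants per arm (Section 8.1). The true rate and the site capture rates are assumptions.

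Observed rate = true rate × capture. Events missed = 150 × true rate × (1 − capture). With equal true rates, apparent RR = CorPath capture ÷ standard capture.

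With a true rate of 8% there are 150 × 0.08 = 12 true events per arm.

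| | Standard, 95% | CorPath, 85% | CorPath, 75% |
|---|---|---|---|
| Observed rate | 7.6% | 6.8% | 6.0% |
| Observed events | 11.4 | 10.2 | 9.0 |
| Missed events | 0.6 | 1.8 | 3.0 |
| Apparent RR | reference | 0.85/0.95 = 0.89 | 0.75/0.95 = 0.79 |

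The gap in observed counts (11.4 − 10.2 = 1.2, up to 11.4 − 9.0 = 2.4) is the between-arm difference, not the number missed.

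The ratio does not depend on the true rate. Over assumed true rates of 2% to 15% (3 to 22.5 events per arm), capture of 70% against 90% gives RR 0.70/0.90 = 0.78 throughout. Equal capture of 90% in both arms gives RR 1.0, with 2.7 to 20.3 events left per arm.

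**The case against.** A reader might infer that the committee receives nothing but site-confirmed MACE, and so can remove events but never add one. The document does not go that far. Section 10.2 gives the committee a wider remit and allows queries to the site. Device- and procedure-related events are recorded whether or not they are MACE, so a peri-procedural event that the site did not call MACE could be forwarded and upgraded. The sentence in Section 7.7.2 also has a regulatory rationale, repeated in Section 7.8.2, and can be read as an SAE-reporting rule rather than a limit on the committee. This stands, and it rules out the absolute reading. It does not supply a route for late events that the site judges neither MACE nor related.

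Site judgement is also constrained: MI has numerical thresholds, ischaemia-driven revascularisation has listed criteria, and undetermined deaths count as cardiac. This narrows the room for discretion, but the unblinded site still applies these rules first.

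Finally, the bias is assumed. Nothing in the protocol shows that capture would differ between arms, or in which direction. In the illustration the shift of 0.8 to 1.6 percentage points is smaller than the standard error of the difference: √(0.076 × 0.924/150 + 0.060 × 0.940/150) = 2.9 points, or 3.0 points with 6.8% in the second term. This too stands. The illustration shows how the effect would work and is not evidence of bias.

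**Conclusion.** The point holds in a limited form. Section 7.7.2 restricts SAE reporting to events judged to be MACE, and that judgement falls first to a site that knows the arm. Adjudication therefore has no assured route to rejected events, above all late ones not called procedure- or device-related. This is inconsistent with Sections 2.4.2 and 10.2.

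The size cannot be derived from the protocol. On the assumed rates, 0.6 (standard) against 1.8 to 3.0 (CorPath) events per 150 would be missed, with an apparent RR of 0.79 to 0.89. That result rests wholly on capture differing between arms; with equal capture only events and precision are lost.

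Two further inferences are not supported: that clinical success is materially distorted, since it uses only in-hospital MACE, and that the MACE comparison will favour CorPath, since the direction was chosen for the illustration.

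**What to change.** Reconcile Section 7.7.2 with Sections 2.4.2, 3.3 and 10.2, so that one rule states what is reported and what reaches the committee. Then require that the following go to the existing committee whatever the site's own classification:

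- every death;
- every repeat coronary angiogram or revascularisation;
- every recorded post-index biomarker value above the protocol's MI threshold;
- every cardiac readmission found in the scheduled health-care resource data.

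The committee, not the site, then decides whether MACE is met. The biomarker trigger must name its threshold, because Section 7.7.2 and Appendix A define MI differently.

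The cost is protocol wording, a trigger rule in the data capture system and some more dossiers. Two limits remain. Post-procedure enzyme testing is discretionary (footnote 3 to the schedule), so the biomarker trigger still depends on an unblinded decision to test. Health-care resource use is in the schedule at Day 30 and Day 365 but not in the visit lists of Sections 7.5 and 7.6, and should be added there if it is to serve as a trigger.
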